### Outcome measures

#### Primary endpoints

The primary outcome is early morbidity, which will be divided into morbidity observed during operation and morbidity observed within 30 days after surgery. Early morbidity will be assessed on POD 30 and classified according to the Clavien-Dindo classification [36].

#### Secondary endpoints

Secondary endpoints will be measured intraoperatively, at daily study visits, and at 1, 3, 6, 36, and 60 months postoperatively. Operative outcomes include operation time, estimated blood loss during operation, and incision length. Pathological outcomes compromise tumor size, length of proximal and distal resection margins, and number of harvested lymph nodes and will be determined postoperatively by pathological examination. Postoperative inflammation and immune response (white blood cells [WBC], neutrophil percentage [NE %], C-reactive protein [CRP], interleukin-6 [IL-6], and tumor necrosis factor-α [TNF-α]) will be measured at 4 hours, 24 hours, and 96 hours postoperatively. Postoperative recovery (time to first ambulation, flatus, liquid diet, soft diet and duration of hospital stay) will be measured daily in-hospital and determined using participant self-report. Pain intensity will be measured using a horizontal visual analogue scale (VAS; a 0 to 10 cm scale with 0 at the left edge representing no wound pain, and 10 at the right edge representing wound pain as bad as it could possibly be) [37] at rest on POD 1, 2, 3, and 5. Additional postoperative analgesic use will be recorded in the CRF. Body image and cosmesis will be measured using the Body Image Questionnaire (BIQ) [38] at 1, 3, and 6 months postoperatively. The 3-year disease-free survival (DFS) and 5-year overall survival (OS) will be measured at 36 and 60 months postoperatively. Confirmation of recurrence will require either the detection of radiologically apparent lesions that increase in size over time or a pathology evaluation. The DFS will be calculated from the time of randomization to the time of either local or distant progression or death (from any cause and in the absence of evidence of recurrence) in participants who have undergone curative surgery. The OS will be calculated from the time of randomization to the time of death from any cause. All measurements and time points are listed in Table 2.

### Data management

Data will be recorded in the CRF by an investigator and reviewed by another investigator for completeness before it is transferred into the trial database. Any missing data will be identified and drawn from source data or from the participants. The CRF will then be transferred into the trial database and double-checked to ensure accurate transfer. Each participant will be given an allocation number according to their randomization. To maintain participant confidentiality, all data will be identified by allocation number, and only the investigators will be able to link the allocation number to the participant’s identification using a list saved separately from the database. All study-related participant information will be stored in a specified investigator’s office in locked filing cabinets. The trial database, photographs and videos will be double saved. In case of withdrawal, follow-up and data collection will continue with the participant’s permission. An investigator will review the database to ensure accurate data collection using descriptive statistics to check for missing data and out-of range values. Any unclear data will be traced to the original medical records. Upon the completion of the trial, all study-related data and trial documents will be archived securely and retained for a minimum of 10 years at Nanfang Hospital.

### Safety and reporting of serious adverse events

All adverse events (AEs, defined according to the Common Terminology Criteria for Adverse Events (CTCAE) version 4.0 [39] and the Accordion Severity Grading System (TASGS) [40]), will be evaluated for severity and causality. Severity will be graded according to the CTCAE [39] and TASGS [40]. Causality will be graded as none, unlikely, possibly, probably, and definitely related to the intervention. Expectedness will be used to evaluate the AEs. Any serious adverse events (SAEs, defined according to the International Conference on Harmonisation (ICH) GCP E6 guidelines [41], TASGS [40], and CTCAE [39]) will be reported to the chief investigator (CI) within 24 h of being noted. If the CI considers an SAE unexpected and related to the study intervention, he will report it to the Medical Ethics Committee (MEC) within 72 h of being notified, and a detailed medical report will be needed within 15 days. The study’s steering committee, which is organized by the authors of the protocol and the Department of General Surgery, Nanfang Hospital, will be responsible for overseeing the study’s progress and safety and will meet to evaluate morbidity and AEs at least three times: after the randomization of 25 %, 50 %, and 75 % of the participants. If the number of treatments related to SAE occurrence is more than 3 % (n = 2) of the sample size in each group, patient enrollment will be terminated immediately, and the MEC will reassess the safety of the trial.

### Statistical methods

#### Sample size

The sample size was determined for the primary endpoint: early morbidity measured on POD 30. Based on our database, the early morbidity rate of CLS for colorectal cancer is 15.2 %; for SILS plus one for colorectal cancer, the early morbidity rate is 11.1 %. The sample size was determined according to the following:Hypothesis: the early morbidity of SILS plus one is not higher than that of CLS (noninferiority analysis).We set the noninferiority margin at 10 %.A one-sided analysis with a type I error (α) of 2.5 % and a power (1-β) of 0.80 was assumed.

Based on these assumptions, a sample size of 90 participants per arm was calculated using the NCSS-PASS (11^th^ edition, NCSS, LLC, Utah, USA). Assuming a drop-out rate of 10 %, the total number of participants needed per arm is 99, resulting in a total of 198 participants for the primary aim.

#### Statistical analysis

The statistical analysis will be performed using SPSS version 13.0 (SPSS, Inc., Chicago, IL, USA). A two-sided p < 0.05 will be considered significant. Descriptive statistics will be used for baseline characteristics. For categorical variables, including the primary outcome, a χ^2^ test or Fisher’s exact test will be applied. For continuous variables, Student’s t test or the Mann-Whitney U-test will be applied. Kaplan-Meier curves and the log-rank test will be used to analyze the OS and DFS differences between the two groups. We do not plan to perform interim analyses. Missing values will not be imputed. Any outcomes of interest analysis will be performed based on the intention-to-treat population and per-protocol population (PPP), and a standard sensitivity analysis will be performed based on the PPP.

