### Objective and hypothesis

The objective of this trial is to evaluate the feasibility, short-term safety, long-term oncological safety, and potential benefits of SILS plus one compared with CLS for the radical resection of rectosigmoid cancer in a randomized controlled trial. The hypothesis is that SILS plus one is feasible for the radical resection of rectosigmoid cancer and offers short-term safety and long-term oncological safety comparable to that of CLS. In addition, SILS plus one provides better cosmetic results and faster convalescence compared with CLS.

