As an essential principle of enhanced recovery, minimally invasive surgery has been championed by a growing number of surgeons [24]. It seems obvious that the SILS plus one technique will enhance recovery compared with CLS by reducing abdominal trauma; however, as the evidence accumulated, there were arguments over whether the reduction of trocar incision is enough to enhance patients’ recovery [1, 13, 14, 34, 45]. To settle the arguments, we will use pain intensity, duration of hospital stay, time to first ambulation, bowel function (time to first flatus), eating habits (time to resuming liquid diet and soft diet) and inflammatory and immune responses (WBC, NE %, CRP, IL-6 and TNF-α) to evaluate patients’ recovery after abdominal surgery [28]. Among the above-mentioned measurements, pain is the most commonly reported symptom and the most subjective one [28]. To transform subjective pain into an objective score, we will use the VAS scale, which is the most sensitive pain scale; compared with the Numerical Rating Scale and the Four-point Verbal Rating Scale, it can discriminate between small changes in pain intensity [46]. We decided to measure patient pain intensity at rest because doing so may eliminate the effect of different levels of mobility on pain intensity. Additionally, we will record the use of additional postoperative analgesics for breakthrough pain, which will influence pain intensity, for further analysis.

The cosmetic advantage of SILS plus one over CLS seems obvious, and it seems to be a permanent advantage of SILS plus one. However, at present, no study available assesses whether reducing the use of abdominal trocars will affect body image, cosmesis, and patient self-confidence. We will use the BIQ to evaluate the patient’s subjective feelings about the cosmesis, and we will use photographs of the incision and the length of incision to supplement the cosmesis evaluation [38].

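### Faster convalescence is a stated hypothesis judged on about 24 comparisons at an unadjusted two-sided 0.05 with no deciding measure; the same gap affects cosmesis, but less

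*Protocol article*

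**What the plan says.** Under Objective and hypothesis, after the comparable-safety hypothesis, the article adds: "In addition, SILS plus one provides better cosmetic results and faster convalescence compared with CLS". The abstract's Discussion paragraph repeats this as part of the hypothesis.

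The main Discussion notes disagreement over whether fewer trocar incisions speed recovery, and continues: "To settle the arguments, we will use pain intensity, duration of hospital stay, time to first ambulation". The list goes on to flatus, liquid and soft diet, and the markers WBC, NE %, CRP, IL-6 and TNF-α.

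Secondary endpoints sets the schedule:
- Recovery: "Postoperative recovery (time to first ambulation, flatus, liquid diet, soft diet and duration of hospital stay) will be measured daily in-hospital".
- Pain: VAS "at rest on POD 1, 2, 3, and 5".
- The five markers: "will be measured at 4 hours, 24 hours, and 96 hours postoperatively".
- Cosmesis: "Body image and cosmesis will be measured using the Body Image Questionnaire (BIQ) [38] at 1, 3, and 6 months postoperatively". The Discussion adds incision photographs and incision length as supplements.

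Statistical analysis gives one threshold: "A two-sided p < 0.05 will be considered significant". Continuous variables are compared by Student's t test or the Mann-Whitney U-test, and outcomes are analysed in both the intention-to-treat and the per-protocol population. The section names no key secondary measure, time point, order or adjustment. Under Sample size, the one-sided 2.5 % error rate and the 198 patients are tied to early morbidity alone.

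**The concern.** The primary analysis can show only that early morbidity is not unacceptably worse with SILS plus one. The positive case for the technique would then rest on convalescence and cosmesis, which the article states as directional hypotheses and not as description. With many measures, one per-test threshold and no statement of which result decides, a chance finding on one marker at one hour, or on pain on one day, could be reported as confirming faster convalescence.

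**Working it through.** **The plan's own figure.** The article states no error rate for the benefit claims, so there is none to reproduce. Its only computed figure is the primary sample size: n = [pC(1−pC) + pT(1−pT)] × (z0.975 + z0.80)² / (margin + pC − pT)². With pC = 0.152, pT = 0.111 and margin 0.10, this is 0.2276 × 7.849 / 0.141² = 89.85, or 90 per arm as stated. The primary calculation is sound and separate from this point.

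**Number of comparisons** (Secondary endpoints; Discussion)
- Recovery times: 5
- VAS pain: 4 days = 4
- Inflammatory markers: 5 × 3 times = 15
- Convalescence total: 5 + 4 + 15 = 24
- Cosmesis: one BIQ score at 3 visits = 3; more if subscales, photographs or incision length are also tested

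One test per time point is inferred from the two-sample tests named. The article does not say it outright, and 19 of the 24 (4 + 15) depend on it.

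**Independent tests, no true difference.** The chance of at least one two-sided p < 0.05 among k tests is 1 − 0.95^k. The chance of at least one such result favouring SILS plus one is 1 − 0.975^k.
- k = 24: 1 − 0.95²⁴ = 70.8 %; 1 − 0.975²⁴ = 45.5 %
- k = 5: 22.6 %; 11.9 %
- k = 3: 14.3 %; 7.3 %

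Expected false positives among the 24: 24 × 0.05 = 1.2, of which 0.6 favour SILS plus one.

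**Correlated tests.** Repeated pain scores and markers are correlated, so the independent figures are upper ones. The article gives no correlations; equal correlation between all test statistics, with critical value 1.96, is an assumption. Chance of at least one false result favouring SILS plus one (nominal 2.5 %):

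| Family | ρ = 0 | ρ = 0.5 | ρ = 0.9 |
|---|---|---|---|
| 24 convalescence tests | 46 % | 23 % | 8 % |
| 5 recovery times only | 12 % | 9 % | 5 % |
| BIQ at 3 visits | 7 % | 6 % | 4 % |

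In either direction (nominal 5 %), at ρ = 0.5: 46 %, 18 % and 13 %. The one-direction figures are the relevant ones, because the harm at issue is a false claim of benefit.

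Analysing each outcome in both populations adds a further, strongly correlated, chance of a false finding. It is not included above.

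**The case against.** The strongest objection is that multiplicity among secondary endpoints is usually left to the analysis plan or the full protocol, neither of which is shown, and that a per-test 0.05 is conventional. As a complaint about missing detail, that would dispose of the point. Here, however, the article itself states the directional hypothesis, lists the measures meant to resolve the recovery question and gives a single unadjusted threshold. An unseen plan could add a hierarchy, but it would have to qualify that rule.

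It is also fair that these endpoints are labelled secondary, that the objective speaks of potential benefits, and that the language about settling arguments is Discussion prose and concerns recovery only. This limits the weight of the point, but the hypothesis wording remains.

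Two stronger readings are tempting. A reader might infer that the plan lets any single significant result confirm the hypothesis. The article does not say so; it lists the measures together and leaves open how they combine, so the family-wise figures apply only under that reading. A reader might also infer that both benefit claims carry an error rate several times 5 %. That fails for cosmesis: BIQ at three visits gives about 13 % two-sided at correlation 0.5 and about 6 % in favour of SILS plus one.

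Finally, the choice of deciding measure is the sponsor's, and nothing in the hypothesis justifies making the cosmesis test wait for a significant convalescence result.

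**Conclusion.** The point holds for convalescence and, in weaker form, for cosmesis. The article does not say which result would establish either claim. If any one significant result may count, the chance of a false finding of faster convalescence is about 23 % over the 24 tests at correlation 0.5, and about 9 % even if only the five recovery times are counted, against 2.5 % nominal in that direction. For cosmesis it is about 6 %.

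These sizes rest on three assumptions: separate testing at each time point, equal correlation over the range shown, and acceptance of any one significant result as support. The primary noninferiority conclusion is untouched, so this is a change the sponsor should make but not a threat to the main result.

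**What to change.** Before anyone compares the arms on these outcomes, amend the statistical section in one of two ways:

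1. Name one deciding measure and time point for convalescence and one for cosmesis, the sponsor's own choice. Test each only after noninferiority on early morbidity is shown, without making one benefit claim depend on the other. For example, split alpha as 0.05 / 2 = 0.025 two-sided per claim.
2. Or apply Holm within each claim's family. The smallest p-value would then face 0.05 / 24 = 0.0021 for convalescence and 0.05 / 3 = 0.0167 for BIQ. Each claim is then held at 5 % two-sided, so the two together could reach up to 10 %.

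Under option 1, label all other recovery, pain, inflammatory and BIQ comparisons exploratory; under option 2, do so for any comparison outside the Holm families. Report these as estimates with 95 % confidence intervals.

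The change is wording only, with no new patients or data. The article reports 82 of 198 patients randomized and plans no interim analysis, so on its own account there was time to do this. The cost is that an isolated significant marker or day can no longer be claimed as confirming the hypothesis, and power for each claim falls slightly if alpha is split.

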## Methods/Design

### Setting

This is a single-center, open-label, noninferiority, randomized controlled trial. The trial is being undertaken at Nanfang Hospital of Southern Medical University, Guangzhou, Guangdong, China, which performs 450 colorectal cancer resections per year. Recruitment began on April 16, 2014, and the trial is expected to proceed for 96 months.

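### The noninferiority primary endpoint is assigned a χ²/Fisher test of equality that never uses the 10 % margin

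*Protocol article*

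**What the plan says.** The Setting section fixes the design: "This is a single-center, open-label, noninferiority, randomized controlled trial". The Sample size section ties the calculation to the primary outcome ("The sample size was determined for the primary endpoint: early morbidity measured on POD 30"), states the aim ("Hypothesis: the early morbidity of SILS plus one is not higher than that of CLS (noninferiority analysis") and adds a margin ("We set the noninferiority margin at" 10 %), a one-sided α of 2.5 % and 80 % power. The planning rates, from the sponsor's database, are 15.2 % for CLS and 11.1 % for SILS plus one. The result is 90 per arm, raised to 99 per arm (198 in total) for drop-out.

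The Statistical analysis section then sets a general threshold, "A two-sided p < 0.05 will be considered significant", and names the primary outcome when it assigns the test: "For categorical variables, including the primary outcome, a χ^2^ test or Fisher’s exact test will be applied". It plans analyses in the intention-to-treat and per-protocol populations. The margin appears only in the Sample size section. Nowhere does the article compare a confidence interval with it or give a criterion for concluding noninferiority.

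**The concern.** In their ordinary form, χ² and Fisher tests take equal rates as the null hypothesis. A noninferiority analysis takes as its null that the new technique is worse by at least the margin. These are different questions, and the planned test answers the wrong one.

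Only two conclusions can be drawn from the test as specified, and neither matches the design:

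- A p-value of 0.05 or more could be taken as noninferiority. That treats lack of evidence of a difference as evidence that the difference is small.
- A p-value below 0.05 in favour of SILS plus one could be required. That is a superiority test, for which the trial is far too small.

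The first reading is a realistic risk. The Discussion reports non-significant survival comparisons (for example p = 0.751, 0.548 and 0.971) as suggesting comparable oncological safety. It criticises those studies for design and size, but not for inferring similarity from non-significance. The endpoint is a safety endpoint, and the Risk-benefit ratio section itself lists increased complications as a possible risk, so a false claim of noninferiority is the costly error.

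A lesser point is that the hypothesis is worded as morbidity being no higher, whereas a 10-point margin can only show that it is not higher by 10 points or more.

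**Working it through.** **Inputs (all from the Sample size section).** CLS rate pC = 0.152; SILS plus one rate pT = 0.111; margin 0.10, read as absolute percentage points; one-sided α = 0.025, z = 1.960; power 0.80, z = 0.842; 90 per arm before drop-out.

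**Step 1: reproduce the stated sample size.** For an adverse outcome, the distance from the expected difference to the margin is 0.10 − (0.111 − 0.152) = 0.141.

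n = [pC(1 − pC) + pT(1 − pT)] × (1.960 + 0.842)² / 0.141²
= (0.1289 + 0.0987) × 7.849 / 0.01988 = 89.85, so 90 per arm.

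This matches the article. The stated size therefore rests on a comparison with the margin, and the absolute reading of 10 % is the one that reproduces it.

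**Step 2: the same size under the planned test.** For a two-sided 5 % test of equality the distance is 0.041. With p̄ = 0.1315:

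n = [1.960 × √(2p̄(1 − p̄)) + 0.842 × √(pC(1 − pC) + pT(1 − pT))]² / 0.041² = 1066 per arm for 80 % power.

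At 90 per arm the same approximation gives 12.5 % power.

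**Step 3: exact operating characteristics at 90 per arm.** For each pair of event counts (x, y), the probability Bin(x; 90, pT) × Bin(y; 90, pC) was summed over the outcomes that meet each rule. The margin rule is that the upper limit d + 1.96 × √[(p̂T(1 − p̂T) + p̂C(1 − p̂C))/90] lies below 0.10, where d = p̂T − p̂C (Wald interval).

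| True rates, SILS plus one vs CLS | χ² p < 0.05 | χ² p ≥ 0.05 | Fisher p ≥ 0.05 | Upper 95 % limit < +10 points |
|---|---|---|---|---|
| 11.1 % vs 15.2 % (planning) | 12.7 % | 87.3 % | 90.9 % | 80.8 % |
| 25.2 % vs 15.2 % (at the margin) | 38.4 % | 61.6 % | 67.9 % | 2.7 % |
| 30.2 % vs 15.2 % (15 points worse) | 67.6 % | 32.4 % | 38.5 % | 0.3 % |

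With the Newcombe interval, the last column is 79.0 % in the first row and 2.6 % in the second. At 99 per arm, χ² is non-significant in 57.5 % of trials at the margin.

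**Step 4: two illustrative results at 90 per arm.**

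- 24 vs 14 events: d = 10/90 = 11.1 points; standard error √[(0.1956 + 0.1314)/90] = 0.0603; 95 % interval −0.7 to +22.9 points; χ² p = 0.068. The planned test finds no significant difference, although an excess of more than 20 points is not excluded.
- 10 vs 14 events: d = −4.4 points; 95 % interval −14.4 to +5.5 points; χ² p = 0.38. Noninferiority is met, and the planned test does not reveal it.

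**The case against.** The strongest defence is that the article never says a non-significant p-value will be read as noninferiority. The Sample size section labels the hypothesis as a noninferiority analysis and gives a margin and a one-sided error rate. The χ² p-value might be only descriptive, with the margin comparison set out in the full protocol or an analysis plan. This does not rescue the text: those items are listed as sample-size assumptions, while the section that governs analysis names the primary outcome and gives it a test of equality. The point concerns what is stated, not what was left out.

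Some of the objections do stand and limit the claim:

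- The figure of about 62 % is conditional on p ≥ 0.05 being taken as noninferior.
- The planned test is not wholly incapable of supporting noninferiority. A significant result favouring SILS plus one would imply it, but this has only about a 12 % chance at the planning rates.
- Two-sided 5 % does not in itself conflict with one-sided 2.5 %. A two-sided 95 % interval compared with a margin is a one-sided 2.5 % test. The fault is the null hypothesis of equality.
- The wording of the hypothesis is secondary, since the margin follows directly after it.
- Requiring success in both analysis sets, and the choice of interval method, are conventions on which statisticians may differ.

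**Conclusion.** The concern holds: the analysis of the primary endpoint is wrong as written and must be corrected. The stated size of 90 per arm fits a margin-based test with about 80 % power and close to 2.5 % type I error. The test actually named has about 13 % power at the planning rates. If its non-significance were read as noninferiority, it would allow a false claim in 61.6 % of trials at the margin (57.5 % at 99 per arm). These figures assume an absolute margin of 10 percentage points, a true CLS rate of 15.2 % and complete data on 90 per arm; the false-claim figures also assume the decision rule just described. The sample size calculation itself is not faulted on this point.

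**What to change.** In the Statistical analysis section, replace the test for the primary outcome with a margin-based rule:

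- Estimate the risk difference in early morbidity, SILS plus one minus CLS, with a two-sided 95 % confidence interval by a named method such as Newcombe or Miettinen-Nurminen.
- Conclude noninferiority only if the upper limit is below +10 percentage points in both the intention-to-treat and the per-protocol sets, which are already planned.
- Keep χ² and Fisher tests for the other categorical variables, and for superiority on the primary outcome only after noninferiority has been shown.
- Reword the hypothesis to say that morbidity is not more than 10 percentage points higher, and state that the margin is absolute.

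The choice of method affects power slightly. At 90 per arm, the Newcombe rule has 79.0 %. A Farrington-Manning score test has about 77 %, and would need 97 evaluable patients per arm for 80 %; the planned 99 per arm would cover that only if almost none are lost.

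The cost is a few sentences, with no extra data or patients. The Trial status section reports 82 of 198 patients randomized as of June 2015, so at that stage the change could be made well before the primary analysis.

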### Recruitment and trial timeline

After being screened for inclusion and exclusion criteria, the potential participants will be verbally introduced to the study by an investigator. A signed written informed consent will be obtained from each patient before his or her inclusion in the study. A copy of the signed consent will be given to the participant, and the original consent will be kept in the hospital. Surgery will be performed within 7 days of patient enrollment or, if it is not, the reason will be recorded in the case report form (CRF). After enrollment, the baseline demographic and clinical characteristics of the participant will be measured preoperatively (Table 2), and any participants who meet the withdrawal criteria (Table 1) will be withdrawn from the trial. The flow of participants and time schedule are presented in Fig. 1.

**Table 2 Tab2:** Preoperative and postoperative outcome parameters and schedule of study visits and follow-up

Measures	Preoperative	Daily in-hospital study visits							Follow-up														
		POD 0^b^	POD 1	POD 2	POD 3	POD 4	POD 5	POD ≥6	M1	M3	M6	M9	M12	M15	M18	M21	M24	M30	M36	M42	M48	M54	M60
Inflammatory parameters (WBC, NE %, CRP, IL-6, TNF-α)	X^a^	X^c^	X^c^			X^c^																	
VAS score			X	X	X		X																
Short-term recovery^d^			X	X	X	X	X	X															
Post-voiding residual urine	X^a^				X																		
EORTC QLQ-C30	X^a^								X	X	X												
EORTC QLQ-CR29	X^a^								X	X	X												
IPSS	X^a^								X	X	X												
BIQ									X	X	X												
Abdominal incision photograph		X							X	X	X												
Physical examination	X^a^								X	X	X	X	X	X	X	X	X	X	X	X	X	X	X
CEA, CA72-4, CA19-9	X									X	X	X	X	X	X	X	X	X	X	X	X	X	X
Chest radiography	X									X	X	X	X	X	X	X	X	X	X	X	X	X	X
Liver ultrasonography										X		X		X		X		X		X		X	
Abdominal and pelvic CT scan	X										X		X		X		X		X		X		X
Colonoscopy or EUS	X										X		X		X		X		X		X		X
Adverse event		X	X	X	X	X	X	X	X	X	X	X	X	X	X	X	X	X	X	X	X	X	X

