^a^Preoperative study visits will be scheduled within 7 days before surgery; ^b^The study visit on POD 0 will be scheduled during and after surgery; ^c^Inflammatory parameters will be measured at postoperative 4 hours, 24 hours, and 96 hours after skin suture; ^d^Short-term recovery, including time to first flatus, time to resuming liquid diet and soft diet, time to ambulating independently and discharge. POD, postoperative day; M, month; WBC, white blood cells; NE %, neutrophil percentage; CRP, C-reactive protein; IL-6, interleukin-6; TNF-α, tumor necrosis factor-α; VAS, visual analogue scale; QLQ-C30, Quality of Life Questionnaire-Core 30; QLQ-CR29, Quality of Life Questionnaire-Colorectal 29; IPSS, International Prostatic Symptom Score; BIQ, Body Image Questionnaire; CEA, carcinoembryonic antigen; CA 72-4, carbohydrate antigen 72-4; CA 19-9, carbohydrate antigen 19-9; CT, computed tomography; EUS, endoscopic ultrasonography

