Postoperative adjuvant chemotherapy will be performed according to the NCCN guideline [29, 30] at the surgeon’s discretion and if the participant is willing. Each participant will be followed up at 1 and 3 months after surgery, then every 3 months for the first 2 years and every 6 months for the next 3 years. Quality of life will be measured with the European Organization for Research and Treatment of Cancer (EORTC) Quality of Life Questionnaire-Core 30 (QLQ-C30) [31], the EORTC Quality of Life Questionnaire-Colorectal 29(QLQ-CR29) [32], and the International Prostate Symptom Score (IPSS) [33] preoperatively and 1 month, 3 months, and 6 months postoperatively. The participants will be evaluated for tumor recurrence using the following methods: physical examination, carcinoembryonic antigen (CEA), carbohydrate antigen 72-4 (CA 72-4), and carbohydrate antigen 19-9 (CA 19-9). Chest radiographs will be obtained every three months for the first 2 years and then every 6 months for the next 3 years. Liver ultrasonography will be performed for the first time at the third postoperative month, then every 6 months for the first 2 years and annually for the next 3 years. Colonoscopy or EUS and abdominal and pelvic CT scans will be performed every 6 months for the first 2 years and then annually for the next 3 years. If the participant fails to return for follow-up visits, he or she will be contacted by phone or email to complete the follow-up data.

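### Outcomes that have a scheduled preoperative value are compared without adjusting for it: the tests are valid but give up precision

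*Protocol article*

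**What the plan says.** The Statistical analysis section of the protocol article gives a single rule for continuous outcomes: "For continuous variables, Student’s t test or the Mann-Whitney U-test will be applied". The significance rule is "A two-sided p < 0.05 will be considered significant". The only use it gives to baseline data is "Descriptive statistics will be used for baseline characteristics". The article names no covariate, change score or longitudinal model.

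Table 2 (Recruitment and trial timeline) marks a preoperative measurement for three groups of outcomes, and its footnote gives the timing: "Preoperative study visits will be scheduled within 7 days before surgery".

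- **WBC, NE %, CRP, IL-6 and TNF-α.** The later measurements follow surgery closely: "Inflammatory parameters will be measured at postoperative 4 hours, 24 hours, and 96 hours after skin suture".
- **"Post-voiding residual urine".** It is measured again on postoperative day 3.
- **QLQ-C30, QLQ-CR29 and IPSS.** The section on perioperative management and follow-up repeats their schedule: "preoperatively and 1 month, 3 months, and 6 months postoperatively".

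Of these, only the inflammatory markers appear under Secondary endpoints. Residual urine and the three questionnaires are scheduled and collected but not listed there, so for them the general rule on continuous variables is the only analysis stated.

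**The concern.** The trial collects a preoperative value of the same measure for nine outcomes and then sets it aside in the comparison between arms. Where baseline and follow-up are correlated, part of the spread within each arm is predictable before surgery. A two-sample test leaves that part in the error term. The confidence interval is then wider, and the power lower, than the collected data allow.

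This matters because the sample size was set for a binary endpoint, early morbidity. Precision for the continuous outcomes was not planned; it is whatever about 90 evaluable patients per arm provide. The inflammatory markers are also among the measures that the Discussion intends to use to judge recovery.

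The point concerns a method that the article states. It is not a detail that the article leaves open for an analysis plan.

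**Working it through.** **1. The plan's own figure.** The only computed figure is the primary sample size. Inputs (Sample size section): morbidity 15.2 % with conventional laparoscopy and 11.1 % with SILS plus one, margin 10 %, one-sided α 2.5 %, power 0.80.

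n per arm = (1.960 + 0.842)² × [0.152 × 0.848 + 0.111 × 0.889] / (0.10 + 0.152 − 0.111)²
= 7.849 × 0.2276 / 0.01988 = 89.8, rounded up to 90.

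This matches the stated 90. The stated 99 is 90 × 1.10; dividing by 0.90 would give 100, a trivial difference. The point made here does not touch this calculation, because the primary endpoint is binary and has no baseline value.

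**2. What 90 per arm gives a continuous outcome.** With two-sided α of 0.05 and 80 % power, the detectable difference for an unadjusted t test is

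(1.960 + 0.842) × √(2/90) = 0.418 SD.

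**3. Effect of using the baseline.** ANCOVA multiplies residual variance by 1 − r². At a true difference of 0.418 SD, power is Φ(2.802/√(1 − r²) − 1.960). The equivalent unadjusted sample size is 90/(1 − r²). The documents give no r, so each row is an assumption.

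| Assumed r | Variance factor 1 − r² | Variance reduction | Power | Equivalent unadjusted n per arm |
|---|---|---|---|---|
| 0 | 1.00 | 0 % | 80.0 % | 90.0 |
| 0.1 | 0.99 | 1 % | 80.4 % | 90.9 |
| 0.3 | 0.91 | 9 % | 83.6 % | 98.9 |
| 0.5 | 0.75 | 25 % | 89.9 % | 120.0 |
| 0.6 | 0.64 | 36 % | 93.8 % | 140.6 |

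At r = 0.5 the detectable difference falls from 0.418 to 0.362 SD.

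**4. What adjustment costs.** One covariate takes one degree of freedom: with 180 evaluable patients, 177 residual degrees of freedom instead of 178.

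**5. Change scores are not a substitute.** If the t test were applied to change from baseline, the variance relative to the unadjusted comparison would be 2(1 − r), taking equal variances at both times. At r = 0.3 this is 1.40, and power falls to 65.8 %. Change scores do worse than the unadjusted test for r below 0.5 and never better than ANCOVA.

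**The case against.** The case against has four main parts.

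- **Validity.** A reader might infer that chance baseline differences, more likely under simple unstratified allocation, would be mistaken for treatment effects. The documents do not support that. Under 1:1 randomisation the error rate of an unadjusted test already allows for chance imbalance. What is lost is efficiency.
- **Size.** A reader might take the upper rows of the table as the expected gain. No correlation is given, and markers sampled hours after major surgery may depend little on their preoperative level. These markers are also the only listed secondary endpoints among the nine outcomes. The factor 1 − r² compares a linear model with a t test and does not carry over directly to the Mann-Whitney option. All of this stands.
- **Importance.** A reader might infer that the hypothesis of quicker recovery rests on these nine outcomes. It does so only in part. The recovery measures named in the Discussion are pain, hospital stay, ambulation, flatus, diet and the inflammatory markers. Only the markers have a scheduled baseline. Quality of life, IPSS and residual urine are not on that list.
- **Condensed text.** The article does not say whether raw values or changes are tested, or how repeated times are combined, and an analysis plan may settle this. That is fair as to those details. It does not remove the point, because the article names the test for all continuous variables and limits baseline data to description.

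Nor does the point extend to VAS pain and BIQ. Table 2 gives neither a preoperative value, so a repeated-measures model for them would be a separate preference.

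**Conclusion.** The point holds as a modest, nearly free improvement in efficiency for outcomes with a scheduled preoperative value. The planned tests are not wrong, and no contradiction in the article is shown.

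The size depends entirely on the assumed r: a variance reduction of 1 % at 0.1, 9 % at 0.3, 25 % at 0.5 and 36 % at 0.6. For the inflammatory markers at 4 to 96 h it may be close to nothing; for the questionnaires it may be larger. No single gain should be quoted. These figures assume a roughly linear relation between baseline and follow-up on the analysis scale and 90 evaluable patients per arm.

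The primary endpoint, its noninferiority comparison and the 198 patients are unaffected.

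**What to change.** For WBC, NE %, CRP, IL-6, TNF-α, residual urine, QLQ-C30, QLQ-CR29 and IPSS only:

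- Prespecify a linear model (ANCOVA) at each scheduled postoperative time, with treatment arm and the preoperative value of the same measure as terms.
- Analyse skewed markers such as CRP, IL-6 and TNF-α on the log scale, with the baseline also logged. State the scale for the other outcomes in advance.
- Report adjusted differences, or ratios for logged outcomes, with 95 % confidence intervals.
- Keep the t or Mann-Whitney test for continuous outcomes without a baseline, including VAS and BIQ.

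The cost is low but not nil. No visit, sample or patient is added. The wording of the analysis changes, and under the Protocol version section a modification must be reported to the investigators, the ethics committee, the participants and the journal. Because missing values are not to be imputed, a patient without a preoperative value would drop out of the adjusted model, so the number affected should be reported. At the last reported count 82 of 198 patients had been randomised, so at that stage the change could be fixed before analysis.
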